### Objectives

The primary objective of the Breastfeeding Trial is to assess the effect of a community-based breastfeeding support programme delivered by health visitors in primary healthcare on the duration of exclusive breastfeeding and social inequality in breastfeeding among women in Denmark. Our hypothesis is that women who receive strengthened breastfeeding support in conjunction with the breastfeeding support offered in the hospital setting will overcome breastfeeding challenges and therefore breastfeed exclusively for a longer period of time. We anticipate that by administering a higher dose of the intervention to mothers who are young or have a low educational attainment, the effects will be even stronger in this group, thereby reducing social inequality in breastfeeding.

We will conduct a comprehensive, multidisciplinary evaluation of the trial by investigating whether the present complex intervention is effective compared with usual breastfeeding support, with respect to:The proportion of women who are breastfeeding exclusively at four months postpartumThe overall duration of exclusive breastfeedingReducing social inequality in breastfeeding

In a process evaluation, we investigate the processes of implementation, specifically:Facilitators of and barriers to implementing the interventionDose, delivery and fidelity of the interventionHow the training programme affects health visitors’ knowledge, self-efficacy and action competencies regarding breastfeeding support

Using a realist evaluation approach, we investigate the relationship between context, mechanisms and outcomes to determine *whether* and *how* the intervention works. The realist evaluation will focus primarily on families in which the mother is young or holds a low educational attainment (i.e., the group that will receive an intensified version of the intervention (see a description of the intervention in Table 2)). More specifically, we will:Investigate important mechanisms of change by examining families and health visitors’ response to and interaction with the interventionAnalyse how contextual factors promote or inhibit the implementation process and the expected mechanisms of change and the potential consequencesInvestigate how the intervention works for mothers who are at an increased risk of early breastfeeding cessation

Finally, in a health economic evaluation, we will assess:The cost-effectiveness of the interventionThe cost-utility of the intervention

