**Development and implementation**
For the adaptation of the previous successful breastfeeding intervention done by Nilsson and colleagues (2017) in hospital setting, an assessment of the needs of families following discharge from hospital after birth and until six months postpartum was carried out. Programme objectives corresponding to findings from the needs assessment formed the basis of the adaptation. In the adaptation process, a participatory approach including health visitor representatives from each of the intervention municipalities was chosen to enhance ownership, to match the organisational structure of the setting (the Danish Health visiting programme), and to ensure implementation in the intervention municipalities. The final intervention programme consisted of a breastfeeding programme for parents and a related training programme for health visitors. In December 2021, 210 health visitors from the 11 intervention municipalities completed a preparatory 3.5-h e-learning course, and in March 2022 they participated in the 15-h physical attendance interactive training programme supported by a written manual. Following training, the health visitors immediately initiated implementation of the programme in their municipalities

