### Sample size and power calculations

For sample size calculation, an estimated eight clusters in each arm were used, totalling 16 clusters. Expected participation rate was 80% with 30% attrition from the first questionnaire at one week postpartum to the third questionnaire at four months postpartum. A power calculation was made using breastfeeding frequencies from 2016 made available from The National Child Health Register [50]. The ambition was to raise the proportion of women breastfeeding at four months in the intervention clusters to the national level. In the design phase, we obtained data on the mean prevalence of breastfeeding at four months in the project regions (49%) and at national levels (56%) in 2016 from the National Child Health Register. The observed difference in the proportion of women exclusively breastfeeding for a minimum of four months corresponds to an odds ratio of 1.32. In the power calculations, an interclass correlation coefficient (ICC) of 0.001, as observed in the previous intervention study [27], was used. Reaching a statistical power of 80% with a 5% significance level is thus achievable provided data are collected from 111 mothers in each cluster. In each cluster, the sample size was extended to ensure that a minimum of 52 mothers were young or had low educational attainment. This yields a power of 80% to investigate an increase in exclusive breastfeeding at four months from 45 to 55% in this subgroup.

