### Statistical methods

We use random allocation to remove any influence of both measured and unmeasured variables on treatment allocation. Before conducting regression analyses, descriptive statistics will be applied to assess selection into the trial, baseline equivalence of trial arms and loss to follow-up.

Regression analyses will be applied when analysing primary outcomes. We will account for the clustered nature of data by using random effects models for binary and continuous outcomes [51] and shared frailty models for analysing time-to-event and recurrent events in continuous outcomes [52]. Intention-to-treat analyses will be conducted. These analyses will include all mother-infant dyads in the relevant trial arms irrespective of their compliance or loss to follow-up. Complete-case analyses will be conducted restricted to observations with available outcome measures [53]. For the intention-to-treat analyses, the survey data will be linked to the Danish national registers including all births; and missing outcome data will be handled by inverse probability weighting and missing covariates by multiple imputation from the registers. The probability weights will be estimated by conducting logistic regressions with outcome data (yes vs. no) as dependent variable and the following baseline variables as predictors: maternal educational, maternal age, cohabitation status, partner’s education, household income, occupational status, maternal smoking status, maternal BMI, and maternal as well as paternal psychiatric histories.

The effect of the intensified intervention will be examined by including an interaction term between treatment arms and a binary indicator of the mother being young or having low educational attainment.

All models will be analysed with treatment alone and adjusted for known predictors for breastfeeding duration collected in the survey (smoking status, maternal age, maternal education, parity, mode of delivery, maternal BMI and cohabitation status) and for design variables used in the randomisation (region of Denmark and number of annual births (< 900 births/year vs. ≥ 900 births/year). As the randomisation will hopefully have distributed the characteristics evenly between trial arms, these adjustments are made to increase the robustness of the effect estimations. Missing predictors will be imputed using multiple imputations and the results compared to the complete case analysis.

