### Multidisciplinary evaluation data

#### Difference-in-Difference design using register data

In the National Child Health Register, municipalities have been required to report data on exclusive breastfeeding since 2011. Difference-in-difference analyses will be applied to estimate the difference in change in proportions breastfeeding at four months, and in average number of weeks of breastfeeding from before (≤ 2021) to after (≥ 2022) the intervention period comparing the intervention and control arm. The advantage of this approach is that it will provide an estimate of the effect if treatment is upscaled to the entire country. The effect of the intensified intervention in the difference-in-difference analyses will be examined by including an interaction term like in the survey analyses. Data from national Danish registers will be retrieved on all mother–child dyads in the included 21 municipalities from 2015 to 2025. This part of the evaluation awaits data availability in the registries which is expected in early 2025 at the earliest. Table 3 provides information on the registers used.

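### The arm-by-social-group interaction measures change in inequality, not the effect of the intensified component, and the 80% subgroup power belongs to a contrast the analysis section does not name

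*Protocol article*

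**What the plan says.** Under Objectives, the article makes reducing social inequality in breastfeeding part of the primary objective. It expects that, because young or low-education mothers receive a higher dose, "the effects will be even stronger in this group, thereby reducing social inequality in breastfeeding".

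Under Intensified intervention, the extra contacts (seven phone calls and one visit) are offered to intervention-arm families in which the mother is under 25 and/or has primary school or vocational training as her highest education. No other group is offered them.

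Under Statistical methods: "The effect of the intensified intervention will be examined by including an interaction term between treatment arms and a binary indicator of the mother". That indicator marks membership of the group just described. The register section carries this over: "The effect of the intensified intervention in the difference-in-difference analyses will be examined by including an interaction term like in the survey analyses".

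Under Sample size and power calculations, the only power statement for this group follows a minimum of 52 such mothers per cluster: "This yields a power of 80% to investigate an increase in exclusive breastfeeding at four months from 45 to 55% in this subgroup". No effect size or power is given for the interaction.

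**The concern.** Two things do not match.

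**Label and design.** In the intervention arm, being offered the intensified component and belonging to the young or low-education group are the same variable. A term built on that variable cannot separate the extra dose from a different response of these mothers to the basic programme.

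**Power and planned analysis.** The trial is sized for an arm comparison inside the subgroup. The analysis section names a comparison of arm effects between subgroups, which is much less precise.

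The stake is interpretation. Reducing inequality is in the title and the primary objective, and the economic evaluation covers the intensified component. Under the present label, a positive interaction would be read as the benefit of the extra contacts. A null one could be read as showing that the extra contacts did nothing or that inequality did not change, from a test with little chance of detecting the effects planned for.

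**Working it through.** **1. What the interaction estimates.** Let B_T be the effect of the basic programme in target-group mothers, E the added effect of the intensified offer in them, and B_O the effect of the basic programme in other mothers. Then

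interaction = (B_T + E) − B_O = E + (B_T − B_O).

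It equals E only if B_T = B_O. The article does not state that assumption, and its Background gives reasons to doubt it: these mothers are described as needing more specific support and as giving up breastfeeding more readily. The register analysis removes pre-existing differences in level, but not B_T − B_O, and more births do not help.

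**2. The article's own power figures.** Inputs from Sample size and power calculations: "an estimated eight clusters in each arm were used, totalling 16 clusters"; "an interclass correlation coefficient (ICC) of 0.001, as observed in the previous intervention study"; "mean prevalence of breastfeeding at four months in the project regions (49%) and at national levels (56%) in 2016"; 111 mothers per cluster overall; at least 52 in the subgroup; 5% level, taken here as two-sided.

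- Overall, 49% versus 56%: 798 effective mothers per arm needed. Design effect 1 + 110 × 0.001 = 1.11; 8 × 111 / 1.11 = 800; power 80.1%.
- Subgroup, 45% versus 55%: 392 needed. Design effect 1 + 51 × 0.001 = 1.051; 8 × 52 / 1.051 = 396; power 80.5%.

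Both reproduce, so the 80% belongs to the within-subgroup arm contrast.

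**3. Power for the interaction in the survey.** Further inputs: a target-group share of 30-40% (Intensified intervention), and 21 clusters in total (Study population), of which 11 are intervention ("210 health visitors from the 11 intervention municipalities completed a preparatory 3.5-h e-learning course"), leaving 10 control. Assumptions: the overall and subgroup planning figures describe one joint scenario, and each cluster has exactly 52 target-group mothers, so its total is 52 / share.

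Worked case, share 35% (148 per cluster, 52 target and 96 other):

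- other mothers, control: (0.49 − 0.35 × 0.45) / 0.65 = 0.512
- other mothers, intervention: (0.56 − 0.35 × 0.55) / 0.65 = 0.565
- interaction: 0.100 − 0.054 = 0.046
- variance, target part, 8 + 8 clusters: 2 × 0.45 × 0.55 / 416 = 0.00119
- variance, other part: (0.512 × 0.488 + 0.565 × 0.435) / 768 = 0.00064
- SE = √(0.00119 + 0.00064) = 0.043; power about 19%

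| Share (total per cluster) | Interaction | Power, 8 + 8 | Power, 11 + 10 |
|---|---|---|---|
| 40% (130) | 5.0 points | 20% | 25% |
| 35% (148) | 4.6 points | 19% | 24% |
| 30% (173) | 4.3 points | 18% | 22% |

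The smallest interaction detectable with 80% power (2.80 × SE) is about 12-12.5 points with 8 + 8 clusters and 10-11 points with 11 + 10. That is at least as large as the whole planned subgroup effect.

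A common cluster intercept cancels in this within-cluster difference, so the ICC is left out. Applying the design effect lowers these powers by about 1 point. The log-odds scale agrees within 1 point.

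**4. Sensitivity to the unstated effect in other mothers**, keeping 10 points in the subgroup and shares of 30-40%, over both cluster counts:

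- gain of 7 points in other mothers: power 10-13%
- gain of 3 points: 35-49%
- no gain: 61-68% (8 + 8) or 73-79% (11 + 10)

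**5. Register analysis.** Assume about 6,000 births per arm after the start (the article expects more than 6,000 families in the intervention arm; the control number is not given), the same interaction, and no clustering over time. Power is then roughly 33-77%, depending on the share and on how much pre-period variance is counted.

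**The case against.** The strongest reply is that an arm-by-social-group interaction is the right test of the hypothesis under Objectives. That stands. A reader might infer that the inequality objective rests on the wrong term. The documents do not support this: the hypothesis is that the effect is larger in one group than in the other, and the interaction measures that difference. Only its description as the effect of the intensified component is wrong.

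A reader might also infer that the 80% is presented as power for the interaction. It is not. The sample size section ties it to 45% versus 55% within the subgroup, and it is correct for that.

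The within-subgroup contrast can be read off the same model, and the sizing suggests it is intended. The choice of reported contrasts and scale may be settled in an analysis plan that is not shown. This is fair as to detail. It does not remove a label in the text that says what the design cannot deliver.

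The 18-25% is soft. It combines a 2016 region-versus-national gap with a separate subgroup scenario, and it covers only the binary survey outcome, not duration of breastfeeding or the register data. It therefore does not show that every inequality analysis will probably be null. Against that, the article says under Outcome measures of the effectiveness trial that the trial was designed around survey measures. Every scenario in step 4 stays below 80%.

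The process and realist evaluations study dose and mechanisms in the target group. They help interpretation but do not supply the missing randomised comparison.

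**Conclusion.** The point holds in a limited form. The survey and register sections attribute to the interaction something this design cannot estimate, because no target-group mothers are assigned the basic programme alone. That conclusion follows from the article's own description and needs no numerical assumption.

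The subgroup power of 80% is right for the arm contrast within young or low-education mothers, a contrast that Statistical methods does not name. For the interaction, survey power is about 18-20% with the 8 + 8 clusters used in planning and 22-25% with the 11 + 10 randomised. These figures rest on joining the two sets of planning rates at a 30-40% share. The firmer statement is that power is below 80% for a 10-point subgroup effect with 52 target-group mothers per cluster, even if other mothers do not benefit at all. More than 52 per cluster would raise it somewhat.

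This is a fault of labelling and stated precision. The interaction should stay, as the measure of change in inequality.

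**What to change.** 1. In Statistical methods and in the difference-in-difference section, describe the interaction as effect modification by social group (change in inequality). Report it as a difference in risk differences with a 95% confidence interval, and drop the claim that it gives the effect of the intensified component.
2. Name the arm contrast within young or low-education mothers, taken from the same model, as the subgroup analysis. Label it basic plus intensified programme versus usual care, and say that the 80% refers to it.
3. In the power section, state that the survey was not sized for the interaction and that its power is low, giving the assumptions behind any figure quoted. Add that a non-significant interaction is not evidence of unchanged inequality.

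The cost is a change of wording and one linear combination from a model already planned, with no new data and no change of design. The downside is a less favourable power statement and a more modest claim about the intensified component.

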### Recruitment to the survey

The health visitors will recruit the families during their first visit after birth. Health visitors have been instructed to inform about the project verbally and in writing in families where the mother meets the eligibility criteria (see information sheet in Appendix A). Enrolment is done by the health visitors who collect families’ consent and help fill in the families’ information in a secure electronic recruitment form. Furthermore, the health visitor assesses whether the mothers qualify for the intensified intervention based on her age and educational level. Participation in the survey and the intensified intervention are independent, i.e., mothers declining participation in the survey may still accept the intensified intervention.

Municipalities will stop recruiting when the required number of mothers with data from the first three questionnaires has been reached, as outlined in the description of the sample size calculation.

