### Data collection

The data collection period commenced on 26 April 2022, in both trial arms. From mid-June it has been possible to assess the full intervention in the intervention clusters, including monitoring the effect achieved by introducing breastfeeding counselling in the pregnancy visit. Local variations will exist in the duration of data collection due to a varying number of births in the clusters. Data collection is projected to end by October 2023 in the municipalities with fewest births.

The questionnaires are distributed to families via personal emails and followed up by two reminders sent by text message (SMS).

Mothers for whom reading and filling out a questionnaire are very challenging are offered a phone call or Microsoft Teams call by a project student assistant who will help them complete the questionnaire. At recruitment, the mother will decide whether to accept or decline this offer.

An overview of the data collection timeline is given in Fig. 3, and Table 3 shows which outcomes and covariates are collected from each survey wave.

**Table 3 Tab3:** Overview of quantitative data collection, source and timepoints

Outcome measures	Survey data						Register data
*Sources*	**Mother**					Partner	
Time point since birth (PP)	One week	One month	Four months	Six months	Twelve months	One month	

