To validate the robustness of the results, the following sensitivity analyses will be performed: First, data will be restricted to mothers having received the full intervention, i.e., including pregnancy visits (June 17 and onwards), to assess the effect of receiving the full intervention compared to mothers having received the intervention without the pregnancy visits (April 26 to June 16); second, observations with no records in registries, most likely an indicator of recent immigration, will be excluded to test whether the effect of the intervention is higher among individuals familiar with the Danish healthcare system than among those who are not familiar with the system; and, third, the worst case scenario assigning no breastfeeding at four months postpartum to all individuals with missing registrations will be used to gauge the minimum effect of the treatment.

The Danish nationwide registries will further allow detailed assessment of selection into the trial (Table 3). Selection into the trial will be examined using register data from 2022, again using inverse probability weighting to assess potential selection effects.

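### As written, the full-intervention sensitivity analysis compares later with earlier intervention mothers, so it confounds pregnancy visits with time and cannot test the randomised result

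*Protocol article*

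**What the plan says.** All references are to the protocol article.

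- Statistical methods introduces the analysis with "To validate the robustness of the results, the following sensitivity analyses will be performed". The first one reads "data will be restricted to mothers having received the full intervention, i.e., including pregnancy visits (June 17 and onwards", and the sentence continues "compared to mothers having received the intervention without the pregnancy visits (April 26 to June 16".
- Data collection: "The data collection period commenced on 26 April 2022, in both trial arms". Of the pregnancy visits it says "From mid-June it has been possible to assess the full intervention in the intervention clusters".
- Recruitment to the survey: "Municipalities will stop recruiting when the required number of mothers with data from the first three questionnaires has been reached".
- Data collection adds "Local variations will exist in the duration of data collection due to a varying number of births in the clusters" and "Data collection is projected to end by October 2023 in the municipalities with fewest births".
- Randomisation states that municipalities with more births have fewer young and less-educated mothers.
- Table 2 (development and implementation) says delivery began straight after the March 2022 training.
- Statistical methods plans random effects for clustering. It also plans models with treatment alone and models adjusted for maternal factors, region and birth stratum (under 900 or at least 900 a year). No calendar-time term is listed.

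**The concern.** A robustness check on a randomised comparison should vary one feature of that comparison and leave the rest in place. This sentence replaces the comparison itself. Control mothers receive neither version of the programme, so on the literal wording they fall in neither group, although concurrent control data exist for both periods.

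Three things then differ between the groups besides pregnancy visits:

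- **Calendar time.** The visits came in at a date, so season and any general trend run with them.
- **Experience.** The early group was seen in the first weeks after training, by health visitors new to the programme.
- **Municipality mix.** Recruitment length depends on births, so the later period leans towards smaller municipalities, whose mothers differ.

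The phrase about having received the programme adds a further doubt. If applied mother by mother, it selects on acceptance after randomisation, which cannot be matched in the control arm.

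At stake is the interpretation of this one analysis. A difference could be credited to pregnancy visits when it reflects time, and a null result could hide a real effect.

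**Working it through.** **1. Who is compared**

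| | Late group | Early group |
|---|---|---|
| Dates | 17 June onwards | 26 April to 16 June |
| Care | programme with pregnancy visits | programme without pregnancy visits |
| Arm | intervention | intervention |
| Control mothers | none named | none named |

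Period and exposure are identical in this table. No model fitted to intervention mothers alone can separate them, whichever maternal covariates are added.

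**2. The plan's own sample size**

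Inputs from Sample size and power calculations: 49% against 56%, 80% power, 5% significance (two-sided assumed), ICC 0.001, eight clusters per arm.

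- Individually randomised size: 798 per arm.
- With design effect 1 + (m − 1) × 0.001 and 8m = 798 × design effect: m = 798 × 0.999 / (8 − 0.798) = 110.7, so 111 per cluster.

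The stated 111 is reproduced and is not in dispute. It serves below as the quota.

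**3. Share of each municipality's sample that is early**

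Inputs: 80% participation and 30% attrition, so 0.8 × 0.7 = 0.56 completers per birth. The early window is 52 days, or 7.43 weeks. Recruitment stops only when enough mothers have the four-month questionnaire, so it continues about 17.4 weeks after the last needed mother is recruited.

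Early share = 7.43 / (quota / weekly completers + 17.4).

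- 900 births: 900 / 52.18 × 0.56 = 9.66 a week; 111 / 9.66 = 11.5 weeks; 7.43 / (11.5 + 17.4) = 0.257, about **26%**.
- 300 births (assumed): 3.22 a week; 111 / 3.22 = 34.5 weeks; 7.43 / (34.5 + 17.4) = 0.143, about **14%**.

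The quota is extended so that each cluster has 52 mothers in the risk group. With 30–40% of mothers in that group, this means 52 / 0.4 = 130 to 52 / 0.3 = 173. The early shares become 24% against 13% at 130, and 21% against 10% at 173. The direction does not change.

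**4. What the mix could do to a crude contrast**

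Assumptions, none from the protocol: quota 149; large municipalities with 1,200 births and small ones with 200; 3 large and 8 small, or 5 and 6, among the 11 intervention clusters; recruitment capped at 31 October 2023 (79.1 weeks).

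- Weekly completers: 12.88 (large) and 2.146 (small).
- Large share, early period, 3 + 8: 3 × 12.88 / (3 × 12.88 + 8 × 2.146) = 69%.
- Late completers per large municipality: (149 / 12.88 + 17.4 − 7.43) × 12.88 ≈ 277. Per small one: (79.1 − 7.43) × 2.146 ≈ 154.
- Large share, late period, 3 + 8: 3 × 277 / (3 × 277 + 8 × 154) = 40%. The fall is 29 points.
- For 5 + 6 the large share goes from 83% to 60%, a fall of 23 points.

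If large municipalities had a breastfeeding rate 3 to 10 points higher (assumed), a crude late-minus-early difference would be between −0.23 × 3 = −0.7 and −0.29 × 10 = −2.9 points with no pregnancy-visit effect at all. The planned effect is 56 − 49 = 7 points. This is before any adjustment.

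**The case against.** The strongest reply is that the sentence can be read more kindly. It speaks of restricting data in order to check results that are arm comparisons, and data restricted to late mothers cannot contain early ones. It may mean refitting the intervention-versus-control model from 17 June and setting it beside the earlier period. That reading is possible, and would be close to the fix below. It is not what the comparison clause says, since that clause names early intervention mothers as the comparator.

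Other replies limit the point, and they stand:

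- **Uptake.** A reader might infer that mothers are selected by individual acceptance. The documents do not establish this. Both groups carry calendar dates, and the text may classify by period alone. The receipt wording still needs correcting, because it misdescribes late mothers who had no pregnancy visit.
- **Municipality mix.** Random effects and adjustment for birth stratum, region, maternal age and education are already planned and address much of this path. Models with treatment alone are also planned, and no adjustment listed addresses time.
- **Size of the mix shift.** Without the questionnaire lag, the 900-birth municipality would appear to be 65% early. The stopping rule excludes that figure, because recruitment continues while four-month questionnaires come in.
- **Only estimate of the rolled-out programme.** A reader might infer this, but it is wrong. The register difference-in-difference analysis also compares the arms and is meant to inform upscaling. Its after-period is 2022 onwards, however, so it does not isolate births after pregnancy visits began.

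**Conclusion.** The concern holds for this one sensitivity analysis. On its wording it is a non-randomised later-versus-earlier contrast within the intervention arm. Calendar time and health-visitor experience are fully confounded with pregnancy visits, and that part cannot be sized from the documents. Municipality mix is secondary: 26% against 14% early at a quota of 111, and a crude distortion of about 0.7 to 2.9 points under assumed municipality sizes and rate differences, before adjustments that would shrink it.

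The analysis therefore cannot validate the robustness of the intervention-versus-control result. It would be going too far to conclude that the trial gives up its randomisation. The primary intention-to-treat comparison keeps all dyads by arm irrespective of compliance and is unaffected.

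**What to change.** Reword the first sensitivity analysis as follows:

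- Define the two periods by date in both arms, regardless of receipt. Birth date is already collected (Table 3).
- Estimate intervention versus control for births from 17 June onwards, and separately for 26 April to 16 June, each against concurrent controls.
- Add an arm-by-period term to the primary random-effects model, with the period main effect.
- Remove receipt of the programme as an inclusion criterion.
- Label any late-versus-early contrast within the intervention arm as exploratory.
- State the remaining limit: the interaction removes time trends shared by the arms, but cannot separate pregnancy visits from growing health-visitor experience, which also occurs only in the intervention arm.

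The cost is a change of wording and a period effect with its interaction in an existing model. No new data are needed. The period-specific estimates will be less precise than the overall one, particularly for the 52-day early window.
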